In PCOS women with ovulatory dysfunction, several nonrandomized trials revealed that repeated acupuncture treatments decreased total testosterone and other sex steroid levels, reduced LH/follicle-stimulating hormone (FSH) ratio, and improved menstrual frequency without negative side effects [17–19]. In a randomized controlled trial (RCT), fourteen acupuncture treatments, with combined electrical and manual stimulation of the needles during 16 weeks and 16 weeks of physical exercise compared with no intervention, improved menstrual bleeding pattern and decreased high levels of sex steroid precursors, estrogens, androgens, and glucuronidate androgen metabolites in women with PCOS [20]. Acupuncture was superior to physical exercise when compared directly after the treatment period. In a quasi-randomized study, daily abdominal acupuncture during 6 months improved menstrual frequency and decreased circulating testosterone more effectively than metformin during 6 months [21]. Recently in another RCT, 12 treatments of true acupuncture were compared with control acupuncture using placebo needles during 8 weeks and similar ovulation rates were found in both groups of women with PCOS [22]. 

Findings from previous clinical and experimental studies indicate that acupuncture may induce ovulation and improve pregnancy in women with PCOS. However, the methodological quality of these studies is of varying quality, and none were designed to investigate pregnancy or more importantly live birth. We sought to address these gaps in knowledge by designing an RCT to examine the effects of acupuncture on live birth in women with PCOS. The objective of the present trial is to test the following three hypotheses in anovulatory women with PCOS: (1) true acupuncture and CC are more likely to result in live birth than control acupuncture and CC, (2) control acupuncture and CC are more likely to result in live birth than true acupuncture and placebo CC, and (3) true acupuncture and placebo are more likely to result in live birth than control acupuncture and placebo CC.

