### 2.3. Randomization

Randomization takes place as soon as the eligibility requirements are met. Participants are randomized into one of the four treatment arms: (1) true acupuncture and CC, (2) control acupuncture and CC, (3) true acupuncture and placebo CC, and (4) control acupuncture and placebo CC by an interactive online computer program in a central office. Using a 1 : 1 : 1 : 1 treatment ratio, there will be 250 women assigned to each treatment group and we expect the dropout rate would be 20%. The randomization is stratified within each of the participating sites by a random block algorithm. The data coordinating center (DCC) statisticians generated and validated the randomization scheme for the study before it was implemented in a web-based database system, and the study coordinator at each participating site logs on the web-based system to retrieve the randomization number after a patient is ready for it. The CC and placebo CC assignments are double-blinded, unknown to patients and study investigators except the DCC data manager. The true and control acupuncture treatments are known only to the TCM specialist (besides the DCC data manager) of the participating site that performs the randomized procedure. 

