### 2.11. Sample Size Calculations

The overall live birth rate for women to receive CC is estimated to be 20% during the 4-month period according to Chinese Obstetrics and Gynecology (Second Edition). Due to lack of existing data on the effectiveness of acupuncture, we cannot rely on the literature for samples size determination. Instead we hypothesize that the order of effectiveness of the treatments is as follows: True acupuncture and CC > Control acupuncture and CC,  control acupuncture and CC > True acupuncture and placebo CC,  true acupuncture and placebo CC > Control acupuncture and placebo CC. The respective live birth rates are projected with 10% difference as follows and the average rate among four arms is 15% (Table 3).

 Using a two-sided trend test and with an effective sample of 200 per group, our study is designed to have >80% power at the significance level of 0.015 (we have three primary hypotheses). The sample size has been inflated from 200 to 250/arm to allow for a dropout rate of 20%, totally 1000 cases for four arms. 

There have been multiple trials to study the effects of CC in PCOS women. The primary aim of this trial is not to reassess the efficacy of CC. The aim is to elucidate the additional efficacy of acupuncture in combination with CC, or acupuncture alone. Acupuncture is compared with CC because CC has been demonstrated to be superior to metformin [4]. The previous study design is used as a role model since it was the best executed and most cited trials in this area. [name] chairs the Steering Committee of this trial, and [name] leads the DCC for another trial using CC in PCOS women. They have considered all related studies, although the power calculation involved inevitably some assumptions. The significance level of 0.015 is approximately 0.05/3 because in this study the overall significance level is controlled to 0.05 after correcting for the multiple comparisons involving three primary hypotheses.

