### 2.12. Data Analysis

The primary outcome is the live birth rate. Secondary outcomes include (1) ovulation rate; (2) ongoing pregnancy rate at gestation 8–10 weeks; (3) multiple pregnancy rate; (4) miscarriage rate: loss of an intrauterine pregnancy before 20 completed weeks of gestation; (5) change in hormonal profile: FSH, LH, T, SHBG, and DHEAS; (6) change in metabolic profile: glucose and insulin concentrations, cholesterol, triglycerides, HDL-C, and LDL-C; (7) side effect profile; (8) change in QOL; (9) change in symptoms of anxiety and depression; and (10) credibility assessments.

The analysis will use an intent-to-treat (ITT) approach to examining differences in the live birth rates among the four treatment arms. Primary efficacy analysis will be done by comparing the treatment groups with respect to the primary outcome of live birth using the Pearson Chi-square test. For the secondary, supportive analysis, we will fit a logistic regression model to compare the treatment arms with respect to the primary outcome of live birth, adjusting for other factors such as randomization stratification of study site and prior exposure to study medications. The analysis of other secondary outcomes measured over time will entail the application of statistical methods that have been developed for correlated data since repeated observations will be made over time on each individual. For secondary outcomes such as hormone levels, a linear mixed-effects model will be fit where the main independent variables will be treatment group, time, and their interaction as well as the designed randomization stratification factors as covariates. Logistic regression models will be used in secondary analyses to evaluate the predictive value of treatment arm, clinical site, prior exposure to CC, body mass index, and other explanatory variables on binary outcomes (e.g., singleton live birth, abortion). Cox proportional hazards models and a Kaplan-Meier method will be applied to compare time to pregnancy in the treatment groups. 

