Sign consent	×										
History	×										×
Urine pregnancy test	×		×	×	×	×	×	×	×	×	
Physical examination	×										×
Transvaginal ultrasound	×										×
Semen analysis	×										
Hysterosalpingogram	×										
Safety eligibility lads	×										×
Fasting phlebotomy for study parameters		×									×
Depression, anxiety, and quality of life questionnaires	×										×
Credibility check questionnaire			×		×						×
Progesterone assay	×			×		×		×		×	×
HCG assay	×			×		×		×		×	×
Acupuncture treatments (twice weekly)			×	×	×	×	×	×	×	×	
Assess adverse events and concomitant meds				×		×		×		×	×

Credibility check questionnaires are completed on the third acupuncture treatment and the last acupuncture treatment.

HCG: HCG concentrations will be measured once a week during the study period. If serum HCG concentration is elevated above 10 IU/L, pelvic ultrasound will be arranged 2 weeks later for the number of the gestational sacs and the viability of the pregnancy.

**Table 3 tab3:** The respective live birth rates in each intervention.

Interventions	True acupuncture	Control acupuncture
CC	*A* = 25%	*B* = 15%
Placebo CC	*C* = 15%	*D* = 5%

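### The stated power above 80% at alpha 0.015 does not hold for hypothesis 1 (acupuncture added to clomiphene): the plan's own rates and 200 women per arm give about 53%

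*Protocol article*

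**What the plan says.** The Introduction of the protocol article lists three primary hypotheses, each between two arms. With A = true acupuncture + clomiphene (CC), B = control acupuncture + CC, C = true acupuncture + placebo CC and D = control acupuncture + placebo CC, they are A > B, B > C and C > D. The first reads "true acupuncture and CC are more likely to result in live birth than control acupuncture and CC".

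Section 2.11 gives one power statement for all of this. The basis is "Using a two-sided trend test and with an effective sample of 200 per group", and the claim is "our study is designed to have >80% power at the significance level of 0.015 (we have three primary hypotheses". The same section explains the level: "The significance level of 0.015 is approximately 0.05/3", chosen to hold the overall error at 0.05 over the three hypotheses. The 200 per arm are inflated to 250 for 20% dropout, and section 2.3 confirms the allocation: "Using a 1 : 1 : 1 : 1 treatment ratio, there will be 250 women assigned to each treatment group".

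Table 3 ("The respective live birth rates in each intervention") projects A 25%, B 15%, C 15% and D 5%.

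Section 2.12 defines the primary efficacy analysis as "comparing the treatment groups with respect to the primary outcome of live birth using the Pearson Chi-square test". It does not mention a trend test.

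**The concern.** The alpha and the power in the same sentence belong to different tests. A level of about 0.05/3 is needed only if three comparisons are each tested and each can succeed or fail. A single four-arm trend test would need no split. A trend test gains power by pooling the gradient across all arms, so a high figure for it says little about any one step of the ordering.

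A vs B asks whether acupuncture adds to first-line CC, which is one half of the aim as section 2.11 states it (the other half is acupuncture alone). If that comparison has far less than 80% power, a true effect of the projected size could easily end as a non-significant result. A reader relying on section 2.11 would then have reason to take that result as evidence of no added benefit.

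**Working it through.** **Inputs.** Two-sided alpha 0.015, so z = 2.432; 200 per arm (section 2.11); rates 25/15/15/5% (Table 3); Pearson chi-square (section 2.12).

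**1. The plan's own figure.** Four-arm trend test with equally spaced scores 1.5, 0.5, −0.5, −1.5 and mean rate 15%:
- Expected statistic: 200 × (1.5×0.25 + 0.5×0.15 − 0.5×0.15 − 1.5×0.05) = 200 × 0.30 = 60
- Null SD: √(200 × 0.15 × 0.85 × 5) = √127.5 = 11.29
- SD under the alternative: √(200 × 0.5925) = √118.5 = 10.89
- Power = Φ((60 − 2.432×11.29)/10.89) = Φ(2.99) = 99.9%; simulation with 200,000 runs also gives 99.9%.

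So the claim of more than 80% is true of the trend test, but that test cannot be where 200 per arm comes from: in simulation it already has 82% power with 75 per arm.

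**2. Each primary hypothesis.** Power = Φ((δ − z·SE₀)/SE₁), with SE₀ = √(2p̄(1−p̄)/n) and SE₁ = √((p₁(1−p₁) + p₂(1−p₂))/n).

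| Hypothesis | Rates | SE₀ | SE₁ | Power | Exact Pearson |
|---|---|---|---|---|---|
| 1: A vs B | 25% vs 15% | 0.0400 | 0.0397 | Φ((0.10 − 0.0973)/0.0397) = 52.7% | 53.4% |
| 2: B vs C | 15% vs 15% | 0.0357 | 0.0357 | 1.5% (both tails; equals alpha) | 1.4% |
| 3: C vs D | 15% vs 5% | 0.0300 | 0.0296 | Φ((0.10 − 0.0730)/0.0296) = 82.0% | 83.7% |

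Hypotheses 1 and 3 both significant: 0.534 × 0.837 = about 45%.

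**3. Sample size for 80%.** n = [z√(2p̄(1−p̄)) + 0.842√(p₁(1−p₁) + p₂(1−p₂))]²/δ².
- A vs B: (2.432×0.5657 + 0.842×0.5612)²/0.01 = 342 evaluable, or 342/0.8 = 428 randomised per arm
- C vs D: 192 evaluable, or 192/0.8 = 240 randomised per arm

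The planned 200 and 250 fit C vs D only.

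**4. Other readings of hypothesis 1.**

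| Variant | Power |
|---|---|
| Alpha exactly 0.05/3, 200 per arm | 54.3% |
| Continuity-corrected test, 200 per arm | 48.0% |
| One-sided 0.015, 200 per arm | 63.0% |
| All 250 per arm contribute | 64.3% |
| One-sided 0.015, 250 per arm | 73.6% |
| Dropouts counted as no live birth (20% vs 12%, 250 per arm; assumption) | 50.3% |
| 20% taken as the rate on CC with control acupuncture (30% vs 20%, 200 per arm; assumption) | 45.1% |
| No multiplicity correction (two-sided 0.05), 250 per arm | 80.0% |

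On a two-sided test, 80% is reached only by giving up both the alpha split and the dropout allowance. A one-sided 0.05 test with 200 per arm gives 80.6%, but that also abandons the stated level and sidedness.

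**5. What the trend test can reject on.** Suppose acupuncture does nothing and only CC works, with A = B = 20% and C = D = 10% (an illustration using Table 3's row means). The expected trend statistic is 200 × (1.5×0.20 + 0.5×0.20 − 0.5×0.10 − 1.5×0.10) = 40, the null SD is 11.29 and the alternative SD is √(200 × 0.625) = 11.18. Power is Φ((40 − 27.47)/11.18) = Φ(1.12) = 87%. A significant trend is therefore no evidence for hypothesis 1.

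**The case against.** The strongest reply is that the sentence is literally true. It names a trend test, that test has about 99.9% power, and nowhere is 80% claimed for A vs B by name. Section 2.11 also presents the three hypotheses together as an ordering, which is the kind of alternative a trend test addresses. Section 2.12 does not say that the chi-square is pairwise; as a single four-arm test with 3 degrees of freedom it would also exceed 99% power.

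Part of this stands. The defect is a mismatch between the powered test and the hypotheses, not a slip in computing the trend-test figure. But neither global test isolates A vs B, the trend test is not the stated primary analysis, and splitting alpha by three makes sense only for three separate comparisons. With two arms, a trend test is essentially the Pearson chi-square, so the 53% remains.

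Three further reservations are fair. The document does not rank hypothesis 1 above hypothesis 3, and hypothesis 3 does have 82%. The 45% scenario is optional, since the quoted 20% for women on CC is also the mean of Table 3's two CC arms, (25% + 15%)/2. The 50% scenario assumes that no dropout delivers. Neither scenario is needed for the conclusion.

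**Conclusion.** The concern holds. On the plan's own rates, alpha and effective sample size, hypothesis 1 has about 53% power, hypothesis 3 about 82%, and hypothesis 2 no power beyond alpha because Table 3 projects no difference between B and C. The single claim of more than 80% therefore holds for one of the three hypotheses that the 0.015 level was set for.

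This rests on reading the Pearson test as applied to each pair, which the three two-arm hypotheses and the alpha split support. Under the variants that keep a level of 0.015 or 0.05/3, power for hypothesis 1 runs from 45% to 74%, with the upper end needing both a one-sided test and all 250 women per arm.

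**What to change.** Keep 1,000 women and replace the power sentence in section 2.11. It should state that, with 200 evaluable per arm and a two-sided Pearson chi-square test at 0.015, the Table 3 rates give about 53% power for A vs B, about 82% for C vs D and 1.5% for B vs C. Delete the trend test as the basis. Reconcile hypothesis 2 with Table 3, which sets B and C equal. Add that a non-significant A vs B result is not evidence of no effect, and that its risk difference will be reported with a confidence interval.

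If an 80% claim is wanted, attach it to a contrast that has it. The pooled acupuncture effect, A and C against B and D (20% vs 10%, 400 per side), has SE₀ = 0.0252 and SE₁ = 0.0250, giving Φ((0.10 − 0.0614)/0.0250) = Φ(1.54), or about 94% at 0.015. The plan does not currently name this contrast as primary, so it would have to be specified before unblinding and given its place in the alpha allocation. It would not answer hypothesis 1 by itself.

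The power restatement costs wording only: no extra women and no change of test or alpha. The price is a less favourable figure for hypothesis 1. It discloses the shortfall but does not remove it, since 80% for A vs B would take 428 women per arm in place of 250.

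### The single-step level of 0.015 for three primary hypotheses is valid but slightly stricter than 0.05/3, and Holm's step-down rule would recover some power at no cost (minor)

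*Protocol article*

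**What the plan says.** The Introduction of the protocol article names three ordered hypotheses on live birth. With A = true acupuncture plus clomiphene, B = control acupuncture plus clomiphene, C = true acupuncture plus placebo and D = control acupuncture plus placebo, they are A above B, B above C, and C above D.

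Section 2.11 bases its power on a trend test, two-sided, taking 200 evaluable women in each arm. It states: "our study is designed to have >80% power at the significance level of 0.015". Further on it justifies that level as a correction for having three hypotheses: "The significance level of 0.015 is approximately 0.05/3 because in this study the overall significance level is controlled to 0.05". Table 3 projects live birth rates of A = 25%, B = 15%, C = 15% and D = 5%.

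Section 2.12 describes the primary analysis as "comparing the treatment groups with respect to the primary outcome of live birth using the Pearson Chi-square test". It gives no per-test threshold of its own, so 0.015 is the only such level in the article.

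**The concern.** Two features of the level invite a question.

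- **The figure.** The stated basis is 0.05 divided by three, but 0.015 is not that quotient rounded in any ordinary way. If 0.015 is the rule, a p-value of 0.016 is negative; if 0.05/3 is the rule, it is positive. A threshold should not depend on which part of the sentence a reader follows.
- **The procedure.** Applying one fixed level to all three tests is the least powerful of the common ways to hold a family-wise error of 0.05. A step-down rule gives the same guarantee and can only add rejections.

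What is at stake is some power on the two comparisons for which Table 3 projects a difference, A vs B and C vs D. The type I error is not in question.

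**Working it through.** **Inputs.** Overall level 0.05, three hypotheses, per-test level 0.015, two-sided testing and 200 per arm (section 2.11); rates 25/15/15/5% (Table 3); Pearson chi-square (section 2.12). The chi-square test is taken to be applied pairwise to A–B, B–C and C–D, matching the three hypotheses.

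**1. The plan's own figure.** Bonferroni: 0.05/3 = 0.01667. Šidák: 1 − 0.95^(1/3) = 0.01695. Neither rounds to 0.015.

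**2. Error actually spent.** The Bonferroni bound is 3 × 0.015 = 0.045. If the tests were independent, the family-wise error would be 1 − 0.985³ = 0.0443. Simulating normal test statistics with the correlation from shared arms gives about 0.042. At 0.05/3 the last two figures are 0.0492 and 0.046. Both levels stay below 0.05.

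**3. Power from correcting the figure alone.** Power = Φ[(|p₁ − p₂| − z·SE₀)/SE₁], with SE₀ = √(2p̄(1 − p̄)/n), SE₁ = √((p₁(1 − p₁) + p₂(1 − p₂))/n), n = 200, and z = 2.432 at 0.015 or 2.394 at 0.0167.

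- A vs B (25% vs 15%): SE₀ = √(2 × 0.20 × 0.80/200) = 0.0400 and SE₁ = √((0.1875 + 0.1275)/200) = 0.0397. At 0.015, Φ(0.068) = 52.7%; at 0.0167, Φ(0.107) = 54.3%. The gain is 1.5 points before rounding.
- C vs D (15% vs 5%): SE₀ = √(2 × 0.10 × 0.90/200) = 0.0300 and SE₁ = √((0.1275 + 0.0475)/200) = 0.0296. At 0.015, Φ(0.914) = 82.0%; at 0.0167, Φ(0.953) = 83.0%. The gain is 1.0 point.
- B vs C (15% vs 15%): the projected difference is zero, so there is no power to gain or lose.

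In sample-size terms, 80% power needs 342 per arm at 0.015 or 334 at 0.0167 for A vs B, and 192 or 188 for C vs D.

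**4. The stated power of more than 80% at 0.015.** A four-arm trend test with 200 per arm has 99.9% power at either level, so the statement holds for the test it names. Pairwise, it holds for C vs D (82.0%) but not for A vs B (52.7%).

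**5. Single-step 0.015 against Holm at overall 0.05.** Holm orders the three p-values and compares the smallest with 0.0167, the next with 0.025 and the last with 0.05, stopping at the first failure. Simulation with 200,000 replicates, binomial counts, 200 per arm, Table 3 rates and Pearson chi-square without continuity correction gives:

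| | Single-step 0.015 | Holm at 0.05 |
|---|---|---|
| A vs B | 53.5% | 60.0% |
| C vs D | 83.7% | 86.7% |
| Both A vs B and C vs D | 44.8% | 53.6% |

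The simulated single-step values lie slightly above those in step 3 because the formula is a normal approximation to discrete counts. With all four rates at 15%, Holm makes at least one rejection in 4.6% to 4.7% of replicates.

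**6. Where the gain comes from.** A separate run put Holm at overall 0.045, so that its first step stays at 0.015. A vs B then went from 53.3% (single-step 0.015) to 58.2% (Holm at 0.045) to 59.9% (Holm at 0.05). Of the 6.6 points gained, 4.9 come from stepping down and 1.7 from using 0.05 in place of 0.045.

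**The case against.** The case for leaving the plan alone is good on several counts.

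- The article says *approximately*. It claims neither equality with 0.05/3 nor that the full 0.05 is spent. A family-wise error of at most 0.045 is control at 0.05, and the power statement uses the same 0.015. A reader might infer a contradiction or a breach of type I error; the text supports neither. This stands in full.
- Correcting the figure alone changes almost nothing (step 3). This also stands.
- Single-step Bonferroni is a standard, valid method, and most of the Holm gain comes from changing the procedure. That is so, and the point is therefore put as an improvement and not as the repair of an error. It does not weaken the case for Holm, which has the same family-wise guarantee under any dependence between tests that share arms.
- The level appears only in the sample-size section, and the analysis plan, which is not shown, may already fix the testing rule. That is possible. The remark is confined to the level that the article itself states and justifies.

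Two stronger readings should also be set aside. A reader might infer that power is given away on all three hypotheses. Table 3 sets B and C both at 15%, so this is not so for the second. A reader might also take strictly ordered rates of 30/20/10/0%, which fit the 10-point steps and the 15% average and would make the Holm gain look larger. Those rates appear nowhere in the article and conflict with Table 3, so they are not used here.

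**Conclusion.** The point holds as a minor one. The level of 0.015 is a valid, slightly conservative stand-in for 0.0167, and the overall 5% error is protected. Correcting the number is worth about 1 to 1.5 points of power. Replacing the single-step rule with Holm is worth about 6.5 points for A vs B, 3 points for C vs D and 9 points for showing both.

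These sizes rest on the Table 3 rates, 200 evaluable women per arm and pairwise Pearson chi-square tests.

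A reader might infer that the strict level explains why A vs B is short of power. It does not: A vs B is about 54% at 0.0167 and about 60% under Holm, still well below 80%. That shortfall goes back to a power statement built on a four-arm trend test, which is a separate matter that this change does not settle.

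**What to change.** Before unblinding, replace the fixed 0.015 with one sentence: the three pairwise Pearson chi-square p-values (A–B, B–C, C–D) are tested by Holm's procedure at overall two-sided 0.05, with the smallest compared with 0.0167, the next with 0.025 and the last with 0.05, stopping at the first non-significant result. If the single-step rule is kept, state 0.0167, or say that 0.015 is deliberately conservative.

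The sentence belongs in the protocol or the analysis plan. It needs no more patients and no new data, and it leaves the family-wise error at or below 0.05. Section 2.12 places general unblinding after all final outcomes are reported, so the change can be made without knowledge of results. If the analysis plan already contains such a rule, it is enough to bring the two documents into line.
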